## Abstract

**Background/Objectives:** Complex regional pain syndrome (CRPS) is a primary pain condition that can develop in a limb after a trauma. Although the condition is rare, it may cause lifelong pain and disability. Evidence-based treatments are limited. Neurogenic inflammation induced by the release of neuropeptides, such as calcitonin gene-related peptide (CGRP), is thought to play an important role in the pathophysiology of CRPS. Recently, drugs targeting CGRP have proven to be effective and well tolerated in the treatment of migraine, but their efficacy in other pain conditions, including CRPS, is unclear. The aim of this study is to assess the efficacy of the anti-CGRP antibody fremanezumab on pain in CRPS. **Methods:** In this randomized, double-blind, placebo-controlled, proof-of-concept study, 60 adult patients with CRPS with a disease duration of 3–36 months are randomized to treatment for eight weeks with fremanezumab 225 mg or placebo administered subcutaneously at a 1:1 rate. The primary objective is to compare the change in pain intensity from baseline to the last week of treatment between fremanezumab and the placebo. Other objectives are to assess pain relief and differences in clinical signs between the groups and to examine if the effect can be predicted by CGRP biomarkers. Adverse events and blinding will also be assessed. **Conclusions:** If found effective, fremanezumab and other anti-CGRP antibodies may emerge as a mechanism-based treatment option for patients with CRPS, which could hopefully improve the overall care of patients with this devastating disease.

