Recently, drugs targeting CGRP have become available and have been shown to be effective in the treatment of migraine [16,17]. However, the role of these anti-CGRP antibodies in other pain conditions is sparsely elucidated. A recently conducted randomized controlled trial on the efficacy of erenumab, an anti-CGRP antibody, on trigeminal neuralgia showed no effect on pain [18]. In a small retrospective study of patients with both migraine and neuropathic pain receiving treatment with anti-CGRP antibodies for their migraine, the patients reported a 41.7% reduction in their neuropathic pain [19]. While the role of CGRP in neuropathic pain is uncertain, the role of CGRP in CRPS is thought to be more crucial. Indeed, preclinical and clinical studies suggest that CGRP mediates pain and inflammation in CRPS [11,20,21,22,23,24]. This makes CGRP a possible target for a mechanism-based treatment approach to CRPS. To the authors’ knowledge, no prior studies have investigated the efficacy of anti-CGRP antibodies on pain in patients with CRPS.

The main aim of this study is to investigate the efficacy of fremanezumab, a drug targeting CGRP, on pain in patients with CRPS. The secondary aims are to assess pain relief and differences in clinical signs between the groups and to explore if the effect can be predicted by CGRP biomarkers.

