### 2.7. Outcomes

Primary outcomes are as follows:1.Difference between groups (placebo vs. active treatment) in the change in self-reported daily ratings of mean ADP intensity in the affected limb from the baseline week (week −1) to the last week of treatment (week 8), as experienced during the past 24 h, rated on an 11-point NRS from 0–10 (0 = no pain; 10 = worst possible pain): the primary outcome is validated and recommended as a first Core Outcome Measurement set for complex regional PAin syndrome Clinical sTudies (COMPACT) and a standard measure of chronic pain in clinical trials [33,34,35,36].

Secondary outcomes are as follows:Difference in pain relief on a 6-point scale—complete, good, moderate, mild, none, or worse—assessed at visits 3 and 4.Difference in the change in the mean CRPS Severity Score (CSS) from the end of baseline to the end of weeks 4 and 8: CSS scores will also be divided into two sub-categories: symptoms and signs [37,38] (assessed at visits 2–4).Differences in the area and intensity of mechanical allodynia, assessed by brushing a soft brush (Somedic) twice at a speed of 1–2 cm/s: the area is measured in cm and the intensity rated on an NRS (0–10) and compared to the unaffected site (assessed at visits 2–4).The relationship between the primary outcome measure and the duration of CRPS (measured in months).

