Tertiary outcomes are as follows:Differences between groups in the Patient Global Impression of Change (PGIC), assessed at visit 4: PGIC measures the patients’ overall change from baseline on a 7-point scale [39].Number of patients with a reduction of ≥30% and ≥50% reduction in the mean ADP in week 4 and week 8 compared to the baseline.Mean values of ADP for all 8 weeks.Differences between groups in the change in the least and worst pain in the previous 24 h, rated on an NRS from 0 to 10, assessed during the baseline week (−1) and the last week of treatment (week 8).Correlations between baseline measures of CGRP nerve fiber density in skin (mm^2^) and immune cells, i.e., Langerhans cells, macrophages, and keratinocytes, inflammatory markers in serum, skin flare response (FR) (measured as a % change in blood flow from baseline over time) [40,41], and treatment outcomes as measured by the mean ADP and CSS (visits 2 and 4).To measure differences from the baseline (visit 2) to visit 4 in inflammatory markers in serum, CGRP nerve fiber length density in skin (mm^2^), and immune cells, i.e., Langerhans cells, macrophages, and keratinocytes and skin FR.To measure differences in passive coping and pain catastrophizing at baseline (visit 2) and at visit 4, assessed using the Pain Self-Efficacy Questionnaire (PSEQ) and Pain Catastrophizing Scale (PCS) [42,43,44].Differences in symptoms of depression and anxiety, pain interference, fatigue, and sleep disturbance, assessed using the Patient-Reported Outcome Measurement Information System (PROMIS-29) short form [45,46,47,48,49,50,51] (visits 2 and 4).Differences in the area and intensity of evoked pain assessed via bedside sensory testing: the pain intensity is measured at the site of maximal pain or as close as possible; cold allodynia is assessed twice using a 20 °C cold Somedic thermal roller, and the same procedure is undertaken for warm allodynia (40 °C); pinprick hyperalgesia is assessed using a pinprick stimulator as the difference in the pain score of 2 stimulations at a control site and the pain site; pain is rated on an NRS (0–10); hyperpathia is assessed via repetitive mechanical pinprick stimulation at a rate of 2 HZ for 60 s, and the pain is rated using an NRS (0–10) at 10 s intervals until the pain ceases [52] (visits 2 and 4).Differences in z-scores and percentages of patients with abnormal scores on the QST, in a reduced version of the protocol by the German Network for Studying Neuropathic Pain [32] (visits 2 and 4): we will measure the CDT, WDT, CPT, HPT, DMA, MDT, MPT, and WUR at the most painful area and at a corresponding non-painful area on the contralateral limb.Differences in extremity edema of the affected and unaffected limb using the gold standard water displacement method based on Archimedes’ principle [53,54] and the circumference measured in cm (visits 2 and 4).Differences in skin temperature of the affected and unaffected limbs using infrared thermometer [55] (visits 2 and 4).Differences in the measurement of Timed Up and Go (TUG) for lower extremities and the Nine-Hole Peg Test (9HPT) for upper extremities (measured in seconds) (visits 2 and 4).The difference in the intensity of the various pain symptoms assessed using the Neuropathic Pain Symptom Inventory (NPSI) [56] (visits 2 and 4).Percentages of patients with adverse effects registered in the treatment period, assessed via open-ended questions in both treatment groups.Differences in pain sensitivity at baseline (visit 2) and visit 4, assessed by using the Pain Sensitivity Questionnaire (PSQ) [57].

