### 2.10. Statistics

Baseline characteristics, including demographics and disease characteristics, will be described using means with the standard deviation (SD) or medians with the interquartile range (IQR) for continuous variables and numbers with percentages for categorial variables. We will use a flow chart to describe the inclusion of patients, including dropouts, loss to follow up, and missing data. We will also report the number of screen failures.

Statistical analysis of the primary outcome will be performed using a *t*-test (parametric) or Mann–Whitney U-test (non-parametric), where applicable. Non-dichotomous primary and secondary outcomes will be performed using a *t*-test or Mann–Whitney *U* test, where applicable. For the primary outcome, the delta values from the average pain intensity in the baseline week to the last treatment week (last 7 days) will be used. Response rates and other dichotomous data are analyzed using Fisher’s exact test or χ^2^ test. Spearman’s correlations coefficient will be used to assess predictors.

The analysis for the primary outcome is the intention-to-treat (ITT) population. The last observation carried forward (LOCF) will be the primary imputation method, and the baseline observation carried forward (BOCF) will be used as a secondary imputation method for those that do not finish the pain diary. Missing data will not be replaced. All patients who have received at least one injection will be encouraged to stay in the study, complete the diary, and come for the remaining visit after 4/8 weeks.

Significance is considered at the 5% level. If there are changes to the original statistical plan, the type of change and the date of the change will be documented, and the document will be signed by the sponsor.

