However, we also acknowledge that there are several limitations of this study. CRPS is an uncommon condition, symptoms and signs can fluctuate and change permanently, and some patients experience spontaneous remission [1,2]. This could make it challenging to reach the number of patients that we aim for within the timeframe of the study. Additionally, based on mechanistic insight, we have chosen to only include patients with a disease duration of maximum 36 months and without spreading of CRPS to other extremities, which may reduce the external validity of the study. When we designed the study, oral anti-CGRP antibodies were unavailable, and it became apparent that it was not possible to make the study drug (an injectable anti-CGRP antibody) and placebo identical in appearance. Therefore, we opted for administration by unblinded third-party personnel, and participants are blindfolded during the injection. Fremanezumab was chosen as pre-filled fremanezumab syringes resemble the syringes used for the placebo as closely as possible in terms of appearance. We cannot exclude the possibility that other anti-CGRP antibodies could be more effective than fremanezumab in reducing pain in CRPS. However, the efficacy of different anti-CGRP antibodies seem to be similar in the treatment of migraine [62]. Moreover, we do not know the optimal dose of fremanezumab for CRPS. The dose of fremanezumab given in the study is the same dose as that used in the treatment of migraine. Finally, as this is a proof-of-concept study, the treatment duration is only eight weeks. Hence, we will not be able to investigate the long-term effects of treatment with anti-CGRP antibodies in CRPS.

With this study, we aim to elucidate the role of neurogenic inflammation in CRPS and to evaluate the effect of anti-CGRP antibodies on pain in CRPS. If found effective, fremanezumab and other drugs targeting CGRP may emerge as a new mechanism-based treatment option for patients with CRPS. This could hopefully improve the quality of life of patients with this devastating pain disorder.

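### The aim is to predict the fremanezumab effect from CGRP biomarkers, but the only stated method, Spearman correlation with outcome and no stated comparison between arms, shows association with outcome

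*Protocol article*

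**What the plan says.** All places are in the protocol article.

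- **Aim.** The Abstract lists as an objective "to examine if the effect can be predicted by CGRP biomarkers". Section 1 (Introduction) repeats it among the secondary aims: "to explore if the effect can be predicted by CGRP biomarkers".
- **Biomarker outcome (section 2.7, tertiary).** "Correlations between baseline measures of CGRP nerve fiber density in skin", together with immune cells, serum inflammatory markers and skin flare response, are to be computed against "treatment outcomes as measured by the mean ADP and CSS (visits 2 and 4").
- **Duration outcome (section 2.7, secondary).** "The relationship between the primary outcome measure and the duration of CRPS (measured in months"). The primary outcome is itself worded as a contrast: "Difference between groups (placebo vs. active treatment) in the change in self-reported daily ratings of mean ADP intensity".
- **Method (section 2.10).** Spearman's "correlations coefficient will be used to assess predictors". The sentence does not say whether the coefficient is pooled or computed by arm. Neither a comparison of the arms' coefficients nor an interaction term is named.
- **Context.** Section 4 (Discussion) notes that "some patients experience spontaneous remission". Section 2.9 assumes a mean reduction of 4 NRS points on active treatment and 2 on placebo.

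**The concern.** In a placebo-controlled trial the effect of fremanezumab is the difference between the arms. A marker predicts that effect only if the difference changes with the marker's level, that is, if the marker–outcome slope differs between the randomised arms.

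One patient's change in pain is not that patient's treatment effect. It also contains natural course, placebo response and regression to the mean. The protocol article expects these to matter: half of the assumed active-arm reduction (2 of 4 points) is also expected on placebo, spontaneous remission is acknowledged, and entry requires a mean baseline score of at least 4. A marker linked to any of these correlates with outcome in both arms and says nothing about who benefits from the drug.

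The trial could therefore report predictors of the fremanezumab effect that perform just as well on placebo. It could also miss a real modifier whose slopes cancel when the arms are pooled. The question is one of the objectives named in the Abstract.

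**Working it through.** **1. The plan's own figure.** Section 2.9 gives a difference of 2, SD 2.5, type 1 error 5% (taken as two-sided) and power 80%. The normal formula gives

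n = 2 × (1.960 + 0.842)² × 2.5² / 2² = 2 × 7.85 × 6.25 / 4 = 24.5, so 25 per arm.

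The t-test version gives 25.5, so 26 per arm, as stated. The sample size is not in dispute. The article gives no power figure or threshold for the predictor analysis.

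**2. Model used for the check.** With T = 1 for fremanezumab and 0 for placebo, and M a standardised baseline marker:

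pain reduction = 2 + 2·T + b·M + c·M·T + error

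The placebo-arm SD is held at 2.5, so the error SD is √(2.5² − b²). A purely prognostic marker has c = 0 and b = r × 2.5. For r = 0.3, b = 0.75 and the error SD is √(6.25 − 0.5625) = 2.38. The values of r are assumptions, because the article gives none; 0.2 to 0.5 is shown. At least 4,000 trials were simulated per setting, each test at two-sided 5%. Ranges in the table show the spread over repeat simulations.

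**3. Prognostic marker with no effect modification: share of trials with p < 0.05**

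| Per arm | r | Spearman, pooled | Spearman, active arm | Interaction test |
|---|---|---|---|---|
| 30 | 0.2 | 27% | 17% | 5% |
| 30 | 0.3 | 51–54% | 32–33% | 5% |
| 30 | 0.4 | 80% | 55% | 5% |
| 30 | 0.5 | 94–95% | 76–78% | about 5% |
| 26 | 0.3 | 47% | 28% | 5% |
| 26 | 0.5 | 91% | 69% | 5% |

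A significant Spearman coefficient here correctly detects an association. It becomes a wrong answer only when it is read as prediction of the treatment effect.

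**4. The opposite error.** Take slopes of −1 on placebo and +1 on active treatment per marker SD (b = −1, c = 2), with 30 per arm. The pooled Spearman coefficient averages about 0 and is significant in 5% of trials, while the interaction test is significant in 88%. This is an extreme case. With no slope on placebo and c = 1, the pooled test is significant in 25% of trials and the interaction test in 30%, so the two differ little.

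**5. What the interaction test can detect.** The standard error of a slope is about 2.5/√n in each arm, so that of the slope difference is 2.5 × √(2/n). The difference detectable at 80% power is (1.960 + 0.842) × 2.5 × √(2/n):

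- n = 30: 2.80 × 0.645 = 1.81 NRS points per marker SD
- n = 26: 2.80 × 0.693 = 1.94 NRS points per marker SD

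Both are close to the whole assumed treatment effect of 2.

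**The case against.** Four points can be made on the other side.

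**The article does not say that the placebo arm is left out.** A reader might infer from section 2.10 that it plays no part in the predictor analysis. The text does not support that: it is silent on pooling and on arms, and a fuller statistical plan may settle it. Spearman coefficients computed in each arm and formally compared could address the question. So it would be too strong to say that Spearman's method can never answer it. What stands is that the article pairs an aim about the effect with a statistic that, as worded, measures association with outcome.

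**Duration is worded as a relationship.** A reader might infer that the trial claims duration predicts the drug's effect, but section 2.7 does not say so. The link is indirect: the relationship is with an outcome defined as a between-group difference. The point is weaker here than for the biomarkers.

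**The analysis is exploratory.** The biomarker correlations are tertiary, the Introduction's verb is explore, and the trial is a proof of concept. This limits the weight of the point, but the objective is still named in the Abstract.

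**The better test is weak.** This stands. Blood samples and biopsies are optional (section 2.11), so fewer patients may contribute than the calculation assumes. Low power argues for a confidence interval and cautious wording. It does not make a correlation with outcome an answer about the treatment effect.

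**Conclusion.** The point holds as a mismatch between a stated aim and the method stated for it. A single Spearman coefficient, pooled or from the active arm, cannot separate a predictive marker from a prognostic one. At 30 per arm, a purely prognostic marker would appear as a predictor in about 27–95% of trials (pooled) or 17–78% (active arm), against about 5% for an interaction test. These percentages rest on assumed marker–outcome correlations of 0.2 to 0.5, complete marker data, normally distributed values and the planning SD of 2.5.

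The case is clearest for the CGRP biomarkers and weaker for duration. It does not touch the primary comparison or the sample size. The change should be made, but the trial's main conclusion does not depend on it.

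**What to change.** For each baseline CGRP marker, listed in advance, and for CRPS duration, add a separate exploratory linear model:

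week-8 mean ADP ~ baseline ADP + treatment + marker + treatment × marker

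- Rank or log-transform the marker if it is skewed.
- Report the interaction coefficient with its 95% confidence interval as the evidence on prediction.
- Show the Spearman coefficients for each arm side by side, as description only.
- Label the results hypothesis-generating.

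The primary t-test or Mann–Whitney analysis stays as it is. If the sponsor prefers to keep correlations alone, the aim in the Abstract and Introduction should be reworded as association with outcome.

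**Cost.** A documented, dated change to the analysis plan, which section 2.10 already provides for, and one additional exploratory model. No new data or patients are needed, and recruitment is expected to run until July 2027, so the change can be made before unblinding. The price is a less definite answer: only slope differences of about 1.8–1.9 NRS points per marker SD are detectable at 80% power, and larger ones still if patients decline biopsies or blood samples.

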### 2.3. Study Visits

All visits are planned at the beginning of the study. Visit 2 is defined as day 1. All study visit days are calculated from this visit date (Table 1).

At visit 1 (screening visit), the patient sits down with a member of the study team, discusses any additional questions, and provides informed consent. After informed consent is obtained, the patient is further assessed for study eligibility. Previous and current medical histories are obtained, and focused neurological and physical examinations are performed to establish or confirm the CRPS diagnosis, and for fertile women, a pregnancy test is taken. The patients are trained to report pain intensity.

Registration in the pain diary starts in the baseline period. If visit 1 is scheduled for more than seven days before visit 2, the patients are instructed to fill out the pain diary for the last seven days minimum preceding visit 2. The patients should have an average daily pain (ADP) intensity of at least 4 and not above 9 on a numeric rating scale (NRS) from 0 to 10 (0 = no pain; 10 = worst possible pain) in the baseline period. This is not revealed to the patient.

At visit 2, the pain diary is used to confirm the inclusion and exclusion criteria (Table 2). Patients are, thereafter, randomized to treatment with fremanezumab or placebo. They receive the first dose of the study drug, and outcomes are accessed (see section on outcomes). Registration in the pain diary continues until the last week of treatment (week 8).

At visit 3, after four weeks of treatment, patients receive the second dose of treatment. An assessment of concomitant medication and any potential side effects is conducted, and blood pressure and pulse are measured. Additionally, a questionnaire on pain relief is filled in. Patients will not receive the second dose of study medicine if the side effects are unacceptable or if they wish to stop for other causes, but all patients who have taken at least one of the two doses of study drug or placebo are asked to continue to participate in the study as described below.

At visit 4, after the treatment period of eight weeks, outcomes are assessed again. An assessment of concomitant medication and any potential side effects and completion of the study is also conducted.

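### The primary diary outcome is to be imputed by LOCF, yet the next sentence says missing data will not be replaced; LOCF is also a weak primary method for this design

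*Protocol article*

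**What the plan says.** Section 2.10 (Statistics) defines the primary variable as a change between weekly averages: "the delta values from the average pain intensity in the baseline week to the last treatment week (last 7 days) will be used". The groups are compared by t-test or Mann–Whitney U test. On population: "The analysis for the primary outcome is the intention-to-treat (ITT) population". On missing values: "The last observation carried forward (LOCF) will be the primary imputation method". BOCF is named as the second-line method where a patient's diary is incomplete. The next sentence is "Missing data will not be replaced". It names no outcome, visit or population.

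Other parts of the article bear on this point:

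- Section 2.3 has the diary running from the baseline week through week 8. Patients who have had at least one dose are asked to stay in the study even if they do not receive the second.
- Section 2.6 gives the two injections at visits 2 and 3, four weeks apart.
- Section 2.7 lists "Mean values of ADP for all 8 weeks" among the tertiary outcomes, so the intermediate weeks are to be summarised anyway.
- Section 4 (Discussion) says that signs and symptoms of CRPS fluctuate, may change for good, and sometimes remit without treatment.

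**The concern.** There are two problems.

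**The rule contradicts itself.** One sentence fills in missing diary data and the next forbids it. An analyst following the article could run the primary test on all ITT patients with LOCF values, or only on those with week-8 diaries. If the choice is made after unblinding, it becomes a data-dependent choice of primary result.

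**LOCF fits this design poorly, whichever reading was meant.** It freezes pain at the last entry. A patient who leaves before visit 3 contributes a one-dose value as the outcome of a two-dose course. The t-test or Mann–Whitney test then treats that value as observed, so the uncertainty of imputation is ignored. BOCF is also a single imputation and does not cure this. The bias depends on who leaves, when, and from which arm.

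**Working it through.** **Inputs from section 2.9.** Expected reduction 4 (active) and 2 (placebo), so a difference of 2; SD 2.5; type I error 5%; power 80%; 26 per arm, raised to 30 for dropouts. The implied dropout is d = 4/30 = 13.3% per arm.

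**Assumption not in the article.** A dropout carries forward a fraction f of the arm's mean week-8 change. f = 0.5 stands for LOCF with half the change realised; f = 0 is BOCF.

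**Step 1: the plan's own figure.** The standardised effect is 2/2.5 = 0.8. The exact two-sided two-sample t-test needs 25.52, so 26 per arm. Exact power is 69.3% at 20, 75.6% at 23 and 80.7% at 26 per arm, against the stated 70, 75 and 80. The sample size reproduces and is not in dispute. At 30 per arm with no dropout, power is 86%.

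**Step 2: equal dropout.** Expected arm change = true change × (1 − d + d·f).

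| | Active | Placebo | Difference |
|---|---|---|---|
| No dropout | 4.00 | 2.00 | 2.00 |
| LOCF, f = 0.5 | 4 × 0.933 = 3.73 | 2 × 0.933 = 1.87 | 1.87 |
| BOCF, f = 0 | 4 × 0.867 = 3.47 | 2 × 0.867 = 1.73 | 1.73 |

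If dropout is unrelated to outcome, available cases have an expected difference of 2.00. The two readings of section 2.10 then differ by 2.00 − 1.87 = 0.13 points on average.

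**Step 3: power under LOCF at equal dropout, 30 per arm, f = 0.5.**

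- If carried values keep SD 2.5, the arm variances are 6.25 + 0.133 × 0.867 × 2² = 6.71 and 6.25 + 0.133 × 0.867 × 1² = 6.37. The pooled SD is 2.56, the effect 1.87/2.56 = 0.73, and power about 79%.
- If the SD of carried values is also halved, the pooled SD is 2.43 and power about 83%.
- Simulation with exactly 4 dropouts per arm gives 80% and 84% for these two cases.

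So power is about 80–84%. Under BOCF it is about 69–75%.

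**Step 4: type I error at equal dropout.** With both arms truly improving by 2, the expected bias is zero and simulated rejection is about 5.0%.

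**Step 5: unequal dropout, f = 0.5, split assumed for illustration (6/30 = 20% versus 2/30 = 6.7%).**

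- More dropout on active: 4 × (1 − 0.2 + 0.1) − 2 × (1 − 0.0667 + 0.0333) = 3.60 − 1.93 = 1.67.
- More dropout on placebo: 4 × 0.967 − 2 × 0.90 = 3.87 − 1.80 = 2.07.
- Both arms truly improving by 2, more dropout on active: 1.80 − 1.93 = −0.13, a false difference against fremanezumab. Simulated rejection is about 5.4–5.6%. Reversing the split reverses the sign.

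**The case against.** The strongest defence is that the conflict is only apparent. The imputation sentence closes by referring to patients who do not finish the diary, so the next sentence may cover everything else: other outcomes, isolated missed days, or not recruiting replacements for dropouts. That is plausible, and one scoping clause would confirm it. But the text states none of these, and an unseen SAP does not help, because the article itself fixes a rule and then negates it.

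The defence also points to retention: patients who miss the second dose are asked to continue (section 2.3), at least two telephone contacts check compliance (section 2.3), and diary completion is encouraged (section 2.10). This stands. If it works, little will be missing and the bias will be small.

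Some stronger readings are tempting but unsupported:

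- *Three rival primary results (LOCF, BOCF, available cases).* BOCF is explicitly ranked secondary, so there are two.
- *LOCF underpowers the trial.* It does so only against the 86% for 30 per arm without dropout. The design target is 80%, and LOCF stays near it.
- *LOCF favours the drug, or seriously inflates false positives.* At equal dropout neither occurs. With all 8 dropouts in one arm and both arms truly improving by 2, simulated type I error is about 6.5–7% at f = 0.5. It reaches about 14% only if dropouts also carry no change at all.
- *A single day's rating will stand in for a seven-day mean.* The article does not state the carry-forward unit, and that detail can properly sit in an SAP.

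**Conclusion.** The point holds on both counts. As written, section 2.10 permits two primary analyses, LOCF-imputed or available-case, and the article offers no way to choose between them. LOCF is a weak primary method here because it assumes stable pain, can present a one-dose value as a week-8 outcome, and counts imputed values as observed.

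The numerical effect is modest under the protocol's own dropout allowance: 2.0 becomes about 1.87 (1.73 under BOCF), with power under LOCF near target and type I error near nominal. With unequal dropout it can go either way, about 1.67 or 2.07 for a true 2.0 in the illustrated split. These figures rest on the assumed fraction of change realised at dropout and, in the unequal case, on an assumed split; the article gives neither. The case for acting rests on the ambiguity of the primary analysis and on a better method being available from data already collected, not on a large demonstrated bias.

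**What to change.** 1. Delete the sentence saying that missing data are not replaced, or limit it explicitly to outcomes other than the primary diary outcome.
2. By dated amendment before unblinding (section 2.10 already provides for documented, sponsor-signed changes), make the primary analysis a likelihood-based mixed model for repeated measures on the weekly mean ADP of weeks 1 to 8. Include baseline ADP, sex (the stratification factor) and treatment by week, and take the week-8 contrast as the primary estimate. Use all diary data, including any recorded after a missed second dose. State the covariance structure in advance with a simpler fallback: an unstructured 8 × 8 matrix has 8 × 9/2 = 36 parameters, which is a lot for 60 patients.
3. Alternatively, use multiple imputation of the week-8 mean from the earlier weekly means.
4. Keep LOCF and BOCF as supportive or sensitivity analyses.

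The cost is wording and a standard model; no new data are needed and the sample size is unchanged. The downside is that the model assumes data are missing at random and replaces the simple t-test or Mann–Whitney test. At least one sensitivity analysis that departs from that assumption should therefore be kept.
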